Behavioural modifications pose few risks to patients, but the efficacy depends on the positivity and persistence of patients [8]. As second-line treatments, antimuscarinic agents can lead to many adverse effects, including dry mouth, blurred vision, constipation, and so on. And the tachycardia, hypertension, headache and other adverse reactions may occur with the beta-3-receptor agonists. Inefficacy and adverse events are the most common reasons for the withdrawal of AM [9]. A retrospective cohort analysis indicated that adherence rates to AM ranged from 27.6 to 40.4% over 12 months [10]. In terms of SNS, a systematic review [11] showed that this treatment could significantly reduce the episodes of urination and urinary incontinence and could reduce the use of pads; however, the complications after implantation include pain at the stimulation site, infection and changes in intestinal function. PTNS is the other treatment for OAB that has been confirmed to improve symptoms [12].

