### Intervention

Participants randomized to the EA group will receive a standardized 30-min EA treatment; the SA group is similar to the EA group except in terms of the current, the size of the needle, and the depth of the needle insertion; the patients in the solifenacin group will be treated strictly following pharmaceutical guidelines. All acupuncture treatment sessions will be performed by Chinese medicine practitioners registered as acupuncturists and who have at least 2 years of clinical experience in acupuncture practice. No participants will receive any other treatments.

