### Electroacupuncture (EA)

According to traditional Chinese medicine theory, the results of previous studies and the opinions of acupuncture experts at Guang’anmen Hospital, China Academy of Chinese Medical Sciences, the following main acupoints will be selected: BL23 (Shen Shu), BL33 (Zhong Liao), BL35 (Hui Yang), and SP6 (San YinJiao). All acupoints are bilateral. The locations of each acupoint conform to the standard defined by the World Health Organization [21].

After sterilizing the acupoint areas, for BL33, a needle will be inserted at a point 1 cm upwards and outwards from the 3rd posterior sacral foramina into the 3rd posterior sacral foramina in a slant and in an inward and a downward direction as well as at an angle of approximately 45–70 degrees to the midline using a 0.30 mm × 75 mm needle inserted approximately 60–70 mm deep. For BL35, a needle will be inserted (needle size 0.30 mm × 75 mm) approximately 60–70 mm deep at a slant in an outward and upward direction. For BL23 and SP6, needles will be directly inserted approximately 25–30 mm deep with 0.30 mm × 40 mm needles. The duration of reinforcing- reducing manipulation of twirling and rotating needle should be used for 1 min to achieve de qi (a composite of sensations including acid, hemp, bilge sensation, warm and pulse, these feelings may even travel along the meridians), which is recognised to be an essential component for acupuncture efficacy. Then electrodes from the EA apparatus will be attached transversely to the needle handles for bilateral BL33 and BL35 with a current intensity of 2 to 6 mA and with a current intensity of 1 to 2 mA for ipsilateral BL23 and SP6. All current intensities will be as high as can be tolerated. The current frequency will be a continuous wave of 10 Hz, and the stimulation will last for 30 min. First, EA will be applied for three sessions per week for a total of 4 weeks, followed by twice a week for 8 weeks a total of 28 sessions over a course of 12 weeks.

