### Solifenacin

Solifenacin will be taken orally at a dose of 5 mg once daily for 32 weeks. It will be suggested that patients who can tolerate the drug should continue to take the drug; the drug should be withdrawn in cases of failure; and patients with severe adverse reactions should stop taking the medicine at any time, which will be recorded.

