	Descriptive analysis of emergency medications and other treatments and drugs used at baseline, during therapy and at follow-up.		A questionnaire will be completed by participants to collect information regarding their other treatments.	Descriptive statistics
	Evaluation of the blinding of acupuncture	Week 12	After the last treatment, the evaluation for the blinding of acupuncture will be tested within 5 min in the EA and SA groups	Descriptive statistics
	EA acceptance assessment	Week 12	After the last treatment, the acceptance of EA will be tested within 5 min with a 5-point scale (‘1’ indicates easily accept and ‘5’ indicates very difficult to accept). Average scores will be calculated.	A chi-square test or Fisher’s test
	Evaluation of the intervention expectation	Weeks 0 and 12	A questionnaire will be completed by participants to evaluate their expectations of the intervention.	A chi-square test or Fisher’s test

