### Sample size calculation

The sample size will be calculated based on previous studies conducted by Zhao Y et al. [14, 25]. A sample size of 420 patients will provide 80% power (α = 0.05) to detect a non-inferiority effect of EA therapy on the primary outcome, assuming a 10% loss. The non-inferiority margin will be 50% of the comparative efficacy between SA and solifenacin. The non-inferiority margin will be set based on our hypothesis that EA will be associated with at least 50% of the difference in efficacy of solifenacin compared with SA.

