### Statistical analysis

Statistical analysis will be conducted by independent third-party professional statisticians. We will use a modified t-test based on the retention of the effect method to analyse whether EA is non-inferior to solifenacin [26]. If the lower boundary of the confidence interval around the mean difference between the numbers in the EA group versus the solifenacin group exceed 50% of the mean difference between the numbers in the solifenacin group and the SA group, then non-inferiority will be claimed. The intention-to-treat (ITT, randomized participants) and per-protocol datasets (PP, ITT participants who received at least one treatment session) will be used to analyse the primary outcome. Missing data will be filled with a multiple imputation method under the missing-at-random assumption. Secondary outcomes will be calculated with observed values. Categorical data will be described by case number and percentage and will be analysed with Fisher’s exact test or the Chi-square test where appropriate. Continuous data will be described as the mean ± standard deviation, median, maximum and minimum values, and comparisons between groups will be conducted by covariance analysis or nonparametric tests where appropriate. A P (2-tailed) value less than or equal to 0.05 will be considered statistically significant. Statistical Package for the Social Sciences (version 13.0; SPSS; Chicago, Illinois, USA) will be used to perform the statistical analysis.

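### The per-protocol set is really a treated set (at least one session), so its agreement with ITT says little about robustness to non-adherence or other OAB treatment

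*Protocol article*

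**What the plan says.** The Statistical analysis section names two sets for the primary outcome. ITT is everyone randomised. The other is defined in a parenthesis: "per-protocol datasets (PP, ITT participants who received at least one treatment session) will be used to analyse the primary outcome". No criterion on adherence, other treatment or protocol deviation is attached. Missing data are to be multiply imputed, and the text does not limit this to ITT.

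Four other places bear on who falls into that set:

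- Electroacupuncture (EA): the course is "a total of 28 sessions over a course of 12 weeks". The sham arm has the same number of sessions.
- Solifenacin: "Solifenacin will be taken orally at a dose of 5 mg once daily for 32 weeks". The section also foresees stopping: "the drug should be withdrawn in cases of failure; and patients with severe adverse reactions should stop taking the medicine at any time".
- Intervention: "No participants will receive any other treatments". Table 1 (Outcome measures) nevertheless lists only a "Descriptive analysis of emergency medications and other treatments and drugs used at baseline, during therapy and at follow-up".
- Sample size calculation: "The non-inferiority margin will be 50% of the comparative efficacy between SA and solifenacin".

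**The concern.** A per-protocol set is meant to show what happens when the comparison is restricted to patients treated largely as planned. In a non-inferiority trial this matters because departures from treatment can move the arms towards each other. A threshold of one session does not restrict the comparison in that way, and the word session has no meaning for a once-daily tablet, so the rule cannot be applied as written to the comparator arm.

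This is not detail left to an analysis plan. The article states a definition, and the definition does not match the label.

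At stake is how the main claim is read. If ITT and this set agree, a reader will take the agreement as reassurance about adherence and other treatment, when the two sets contain nearly the same patients. The article describes no other primary-outcome analysis that addresses either problem.

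**Working it through.** **1. What separates the two sets.** Only never-starters leave. Their number is not stated. If 1, 2, 3 or 5% of 420 never start (assumed), the set holds 416, 412, 407 or 399 participants, that is 95 to 99% of ITT. The exposure needed to qualify is 1/28 = 3.6% of the acupuncture course. Early solifenacin stoppers and users of other OAB treatment all remain. A patient with one session and no week-12 score could also remain, with an imputed outcome.

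**2. The plan's own sample size.** The article gives no SD and no expected change in any arm, so 420 cannot be rebuilt from its inputs. The loss step is consistent: 140 × 0.90 = 126 evaluable per arm, and 3 × 140 = 420.

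**3. The test.** With effects scored as improvement, 50% retention means EA − SOL > −0.5(SOL − SA). This is the contrast ψ = EA − 0.5·SOL − 0.5·SA > 0.

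- In SD units, SE(ψ) = √[(1 + 0.25 + 0.25)/126] = √(1.5/126) = 0.109.
- Let d = (SOL − SA)/SD under full adherence. If EA equals solifenacin, ψ = 0.5d. Taking 80% power at one-sided 0.025 (my reading of the two-tailed 0.05), 0.5d/0.109 = 1.960 + 0.842, so d = 0.611. This value is back-solved, not documented.

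**4. Direction of the bias.** Suppose a fraction f of the solifenacin arm falls to sham level.

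- EA − SOL rises by f·d, which helps EA.
- The margin 0.5(SOL − SA) shrinks by 0.5·f·d, which works against EA.
- The net gain for EA is 0.5·f·d.

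**5. Size when EA truly retains exactly 50%.** Here ψ is zero under full adherence and the false-claim rate is 2.5%. With solifenacin stoppers, the shift is 0.5·f·d/0.109 = 2.80·f, and P = 1 − Φ(1.96 − shift).

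| Scenario (fraction affected) | 10% | 20% | 30% |
|---|---|---|---|
| Solifenacin stops, EA fully adherent: shift | 0.28 | 0.56 | 0.84 |
| – false-claim rate | 4.6% | 8.1% | 13.1% |
| EA stops at half the solifenacin rate (shift 1.40·f) | 3.4% | 4.6% | 6.2% |
| EA patients take other treatment of solifenacin-sized effect (shift 2.80·f) | 4.6% | 8.1% | 13.1% |
| EA and solifenacin diluted equally (shift 0) | 2.5% | 2.5% | 2.5% |
| Sham patients take such treatment (shift −2.80·f) | 1.3% | 0.6% | 0.3% |

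Under equal dilution, power when EA truly equals solifenacin falls from 80% to 71, 61 and 50%.

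Because the one-session set keeps these patients, it shows the same behaviour as ITT in every row.

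**The case against.** The strongest reply is that the harm is easily overstated, and several parts of that reply stand.

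- A reader might infer that non-adherence in general pushes this trial towards non-inferiority. It does not. The margin comes from the concurrent solifenacin–sham difference, so equal dilution leaves the error rate at 2.5%, and other treatment in the sham arm works against EA.
- A reader might think the lower comparator and the shrinking margin both favour EA. The shrinking margin is stricter and cancels half of the gain.
- A reader might call agreement between the two sets guaranteed by construction. It is near-automatic only if never-starters are few. The number is not given, and with an open drug arm it need not be negligible.
- A reader might carry the Background's "adherence rates to AM ranged from 27.6 to 40.4% over 12 months" over to the primary endpoint. That figure comes from a retrospective cohort over 12 months; the endpoint is at 12 weeks. It makes differential stopping plausible but does not size it.
- The article does not say why both sets are analysed, so no intention to check adherence should be attributed to it.
- A strict adherence cut has its own risk. The article directs that solifenacin be withdrawn for failure, and it states no matching rule for acupuncture. Excluding everyone with low drug exposure could selectively remove solifenacin failures who followed the protocol. The figures above do not show that a per-protocol set would restore 2.5%.
- ITT remains a stated primary-outcome analysis, other treatment is prohibited and tabulated, and stopping for severe reactions is recorded.

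None of this turns a one-session threshold into a per-protocol definition, or makes it applicable to a tablet.

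**Conclusion.** The definition is wrong for its label, on the wording alone. The set is a treated set, undefined for the solifenacin arm, and cannot serve as a check on non-adherence or other OAB treatment. Agreement with ITT should carry little weight.

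The consequence is conditional. The non-inferiority test leans towards EA if solifenacin non-adherence exceeds EA non-adherence, or if EA patients take other OAB treatment. The 4.6, 8.1 and 13.1% figures are the one-sided case. They rest on 126 per arm, a back-solved difference of 0.611 SD, one-sided 0.025, EA at exactly 50% retention, full EA adherence and stoppers at sham level. If EA patients also stop, the rise is smaller. The documents do not support a claim that the trial's result will be biased towards non-inferiority.

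This is a should-fix point: ITT stands, but its only stated companion analysis does not do what its name promises.

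**What to change.** 1. Rename the present set 'treated set' and give it a criterion that works in each arm: at least one session, or at least one dose.
2. Before unblinding, define a true per-protocol set for week 12: arm-specific exposure (sessions attended; solifenacin taken), no prohibited OAB treatment before week 12, and no major deviation. The trial team should set the thresholds.
3. State explicitly how patients withdrawn for failure or adverse reactions, as the Solifenacin section directs, are classified in this set, so that they are not selectively dropped from one arm. This is an analysis rule and changes no one's treatment.
4. Report this set beside ITT, and interpret any discordance before claiming non-inferiority.

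Cost: mostly wording. The other-treatment questionnaire is already planned. Sessions attended and tablets taken need recording if they are not already captured; the article does not say that they are. The set is selected after randomisation, so it complements ITT and cannot replace it. It will also be smaller, with wider intervals: on the inputs above, power is about 75% with 112 per arm (0.5 × 0.611/√(1.5/112) − 1.96 = 0.68) and about 70% with 100 per arm (0.5 × 0.611/√(1.5/100) − 1.96 = 0.53). Trial status reports 23 recruited, so at that stage the change could still be made early.

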## Discussion

OAB is a common disease among people in many countries. The economic burden in terms of managing OAB is substantial according to research conducted in the following six countries: Canada, Germany, Italy, Spain, Sweden and the UK [27]. Acupuncture is a traditional Chinese medicine therapy that has been proven effective for lower urinary tract dysfunction with advantages of minimal adverse effects, being non-toxic, having a low socioeconomic burden [16, 28]. However, there have been few appropriately designed randomized control trials that have provided strong supporting evidence about the effectiveness of acupuncture for the treatment of OAB worldwide. Thus, in this non-inferiority, randomized controlled trial, we intend to compare the efficacy of EA versus solifenacin to evaluate whether EA treatment is effective in the management of OAB and its clinical value. If the effect of EA is non-inferior to that of solifenacin, it may be a reasonable option in patients with OAB as a complementary and alternative approach.

To assure the reproducibility of the study, we have carefully designed this RCT and have included thorough details about the plan for implementation, aiming to offer trustworthy evidence for the effects of EA on OAB. Computer-generated randomization and central randomized allocation concealment will be adopted to minimize selection bias, and blocked randomization will be applied to ensure prognostic balance between groups. Those outcome assessors, data managers and supervising staff will be blinded to the group allocation.

One of the limitations of this trial design is the non-blinding of the EA group and solifenacin group. Due to the characteristics of acupuncture and the drug, it is impossible to blind the participants and acupuncturists. The other limitation is the use of SA as a control in this trial. Because no ideal placebo-acupuncture exists [29], choosing an appropriate sham acupuncture as a control is important. In this trial, minimal use of EA for non-acupoints will be used as the SA control. In order to blind the patients successfully and the convinience of the operation, all patients will receive acupuncture with prone position, and expose the waist, hips and double lower limbs on the bed curtained off. They will not be able to see the differences of manipulation. During acupuncture, patients will be required to have quiet rest to avoid talking to each other. Doctors will give patients uniform instructions to reduce the impact of psychological suggestions on the efficacy of acupuncture.

In conclusion, under strict quality control, we expect that the results of this study will provide high-grade evidence to determine whether the effect of EA is non-inferior to solifenacin for improving the symptoms of patients with OAB.

### Trial status

This study is currently ongoing. The study commenced on September 2019, 23 participants have been recruited, and the anticipated end date is 30 June 2021.

## Data Availability

The datasets used and/or analysed after completing the current study will be available from the corresponding author upon reasonable request.

## Abbreviations

OAB: Overactive bladder
ICS: International Continence Society
AUA: American Urological Association
AM: Antagonists selective for receptor M
PTNS: Percutaneous tibial nerve stimulation
SNS: Sacral nerve stimulation
EA: Electroacupuncture
OABSS: Overactive bladder symptom score
CI: Confidence interval
RCT: Randomized controlled trial
SA: Sham electroacupuncture
STRICTA: Standards for reporting interventions in clinical trials of Acupuncture
CRF: Case report form
OAB-q: Overactive bladder questionnaire
ITT: Intention-to-treat
PP: Per-protocol
